#### 3.1.3. Quality of Life

Regarding psychological variables, participants will fill in the Spanish version of the INICO-FEAPS Scale [41], aimed at assessing quality-of-life-related personal outcomes from the perspective of the person with an intellectual disability. It is a reliable tool for the target population, with an internal consistency of ∝ = 0.937 (Cronbach’s alpha) [41]. This self-report tool consists of 72 items assessed by a four-point Likert-type scale (from 1 = Never to 4 = Always) and distributed among 8 dimensions: self-determination (SD), rights (RI), emotional wellbeing (EMO), social inclusion (INCL), personal development (DEV), interpersonal relationships (RE), material wellbeing (MAT), and physical wellbeing (PHY). Each dimension is composed of nine items, and some scores are reversed because of the wording. Each subscale score is calculated by summing up the score of its nine items, and a total score is then calculated by summing up the subscale scores. Since subscales can be scored independently, we will only include in the study the four dimensions that we consider most appropriate to reflect the possible effects of a forest bathing intervention (EMO, DEV, RE, and PHY). This will be easier to handle for participants, especially those who have short attention spans. The reference educators will accompany participants when completing the questionnaire to provide support in case of doubts or difficulties in understanding. Cronbach’s alpha reliability for each sub-scale is the following: EMO (∝ = 0.792), DEV (∝ = 0.703), RE (∝ = 0.798), PHY (∝ = 0.659) [41].

### 3.2. Environmental Comfort

The physiological equivalent temperature (PET) value [42] and an individual questionnaire about thermic perception will be used to evaluate environmental comfort. Calculation of PET requires measuring ambient temperature and humidity, radiant temperature, wind speed, solar irradiance, and illuminance in the place where the activity happens [43], plus an estimation of user clothing and activity. An Ahlborn 2892-9 portable weather station fitted with a radiant temperature sensor (model FPA805GTS), a humidity and temperature sensor (model FHA646AG), and an actinometer (model FLA628S) will be used to record those environmental parameters during each session. The sensors will be set at 150 cm above ground level on an anchored tripod, and their readings integrated at 10-min intervals. The station will be concealed in close surroundings to the participants, to avoid distracting them from the activity. Registers within a radius of 50 m of the area of interest are considered valid. Regarding thermal sensation, participants will fill in a short questionnaire replicating tools used in published studies [44,45].

### 3.3. Fidelity, Barriers, and Facilitators of the Implementation Process

This data will be collected during the sessions in a non-participant observation field diary following an established common structure for each session report, including: (1) description of the session: name of the person in charge of the guidance, chosen route; (2) description of the ongoing process of the session: duration of each stage, an example of activities and materials delivered, and participants’ responses to them; (3) difficulties or climate considerations noticed during the activity or through participant comments. There will be two non-participant observers from the research team from the participant university and two from the center’s educational team.

## 4. Detailed Procedure

### 4.1. The Forest Bathing Intervention

The forest bathing intervention follows the method developed by Forest Therapy Hub [46] from the base approach proposed by [name] and [name] [47,48]. It consists of 11 consecutive sessions (one session per week), each one lasting about 2 h (Figure 2). Each session involves an easy walk through a forest area, interspersed with non-intrusive activities of contact with the surrounding nature aimed at fostering mindfulness and the use of the five senses. Three routes have been designed and prepared for their use with this population: two of them in oak forests and a third one next to a river (Figure 1B). To adapt the process to participants’ characteristics and needs, the sessions have been designed cooperatively by the center’s education team, technicians, psychologist and social worker, and the main researchers of this project. Therefore, the process of forest bathing is agreed upon by the whole team and customized in terms of time, routes, physical demand, and reflective questions during the activities. For example, the guides will help the participants through reflective activities to identify and share their thoughts, as this is usually a challenging process for many of them. Also, the team selected routes with very gentle or no slope and will prepare the path to minimize any possibility of stumbling or slipping while walking.

Sessions will be carried out in groups of 6 to 9 participants and guided by a trained guide (see training description and guides characteristics in Section 4.2). Although participants will experience different activities each week (Figure 1C), sessions will always follow the same sequence of four parts (Figure 2). The first phase introduces the activity, the setting, and the participants. Secondly, the “initial phase” focuses on disconnecting from every thought that is not the present moment. Thirdly, the “intermediate phase” is centered on connecting to the environment. Lastly, the “final phase” aims to integrate all the experiences of the previous phases. In all the phases, participants are invited to share their impressions with the rest of the group.

### 4.2. Forest Guide Training

A group of eighteen people has been trained as forest bathing guides. Ten of them are educators (responsible for programming the center’s pedagogical daily activities and supervising users), and eight are technicians (foresters and environmentalists) drawn from the other institutions involved in the project and familiar with the characteristics of the center and the people enrolled in it. The training consisted of a 96 h course led by an international expert in a professional capacity in forest bathing [46]. The content was focused on the design of forest bathing practices and on specific activities to carry out during the intervention, as well as some strategies to lead groups in this context. The training program involved five full-time days of theory and practice (40 h) in place and a practice period consisting in self-paced exercises, guiding two of the intervention's forest bathing sessions, and three follow-up online sessions to review the walks and to support the adaptations (56 h). We found no programs specifically tailored for guiding people with disabilities, so the guides were trained in forest bathing from a generic point of view in that sense. Since the cooperative’s educators already have the expertise in working with this type of individual, they will be the ones in charge of guiding the participant groups. The other guides (foresters and environmentalists) will act as support guides when necessary, always accompanied by an educator.

### 4.3. Ethics

The research ethics committee approval has been obtained from the University of Navarra Ethics Committee (code 2021.042). In the approval process, people with intellectual disabilities were considered to be a vulnerable population. For that reason, the information and consent documents were adapted to their needs by simplifying the writing where necessary and using accessible fonts and formats. Also, legal guardians were involved when applicable in the information and consent process. The permission to reach the center’s participants and workers for carrying out the study has also been obtained from the social cooperative through a signed formal letter. The emWave^®^ Pro Plus license has been purchased with the project funding and the INICO-FEAPS scale is an open-access instrument, and so the author’s permission has not been necessary. All participants will be given information about the study procedures and written consent will be obtained from subjects or their legal tutors before the project starts. Anonymity of participants will be safeguarded by assigning a participant code to each of them.

## 5. Expected Results

It is hypothesized that participants who complete the forest bathing intervention will report significantly:Higher quality of life.Reduced levels of blood pressure.Improved psycho-physiological coherence parameters.

## 6. Data Analysis Plan

R software will be used for quantitative data entry and analysis. The statistical analysis will follow a per protocol analysis approach, where missing data will not be included [49,50]. Descriptive statistics, including the frequency distribution and central tendency measures, will be used to summarize and describe the socio-demographic data. Sex, age, medication, and degree of intellectual disability will be analyzed as potential confounders. When normal distribution is achieved, a one-way ANOVA test with a level of significance at 5% will be performed to compare mean differences in paired data across the time. Otherwise, the Friedman test will be used as its non-parametric alternative. Effect size based on Cohen’s d [51] will be also calculated.

Qualitative data analysis for the observations registered in the field diary will be based on content analysis [52] where categories and thematic units will be identified.

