### 2.2. Sample Size Determination

Conventional sample size calculation does not apply due to the exploratory nature of the investigation at this stage of the MRC framework, whose main objective is to explore the preliminary efficacy and feasibility aspects of the implementation process [31]. Nevertheless, we considered that a minimum of 30 would be sufficient to give a reasonable indication of the likely effect size in line with other similar papers [32,33,34]. Assuming attrition of 15%, the study seeks to recruit 35 persons (the number of eligible participants with intellectual disabilities enrolled in the occupational center where the study will be carried out).

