## 3. Data Collection Plan

Once participants sign the consent, the baseline measurement will take place before the first forest bathing session (two weeks before the intervention). The same set of measures will be collected right after finishing the last session (posttest) and seven months after completing the intervention (follow-up) (Figure 2). The timelapse before the follow-up data collection responds to a study recommendation of gathering mid- and long-term measures after a forest bathing-based intervention [36,37]. Since this is an exploratory study, we will take just the mid-term follow-up measures, as we understand that the long-term ones correspond to a full study. Although the general duration recommendation for mid-term is 6 months after finishing the intervention [32], we will consider 1 month of grace period before or after the 6 months target assessment time to take into account significant events in context. 

Two researchers will collect the physiological and psychological data in one allocated room in the occupational center. This room will be a big open area with windows overlooking the forest and furnished with coaches, exercise mats, tables, chairs, office, and craft supplies. This room will be familiar to participants, as they will perform different daily activities and meetings there. The three data collection events will take place in the same room.

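### The only stated efficacy analysis is per protocol with missing data left out, so the pre-post effect size may be biased, plausibly upward

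*Protocol article*

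**What the plan says.** Section 6 (Data Analysis Plan) states one approach for the quantitative outcomes: "The statistical analysis will follow a per protocol analysis approach, where missing data will not be included". It names no analysis of all enrolled participants beside it.

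The test for change is then fixed: "a one-way ANOVA test with a level of significance at 5% will be performed to compare mean differences in paired data across the time". If normality fails, "Otherwise, the Friedman test will be used as its non-parametric alternative".

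Section 3 sets three measurement occasions: baseline, directly after the last session, and seven months after the programme ends.

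Section 2.1 aims to estimate preliminary efficacy in adults with intellectual disability and to examine feasibility. Section 5 narrows the hypothesis: it expects that "participants who complete the forest bathing intervention will report significantly" better outcomes. Section 2.2 says of the sample that "we considered that a minimum of 30 would be sufficient to give a reasonable indication of the likely effect size", and allows for 15% attrition with a target of 35. Section 2 places the study in the feasibility phase, which is to support the decision on moving to the next stage. The Limitations section mentions sample size and the absence of a control group, but not attrition.

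**The concern.** Two kinds of participant can drop out of the estimate although useful data on them exist.

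- **People who stop the sessions.** They may still be at the centre and be measured at posttest, but a per-protocol set leaves them out.
- **People who miss only the seven-month visit.** The Friedman test works on complete blocks, and a standard repeated-measures ANOVA drops anyone who lacks a visit. With missing data not included, such a person would ordinarily be lost from the baseline-to-posttest contrast as well.

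In a single-group design nothing offsets selective loss: if those who leave differ in their response, the difference goes straight into the estimated change. It is plausible that people who like or tolerate the sessions least are likelier to stop, which would push the estimate upward. At stake is the effect size passed to the next stage. A full-scale trial sized on an inflated completer effect would be too small. A completer estimate also answers a narrower question than the first objective, which is not limited to completers.

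**Working it through.** **1. The plan's own figure.** Inputs from Section 2.2: minimum 30, attrition 15%, target 35.
- 30 / (1 − 0.15) = 35.3, rounded up to 36.
- 30 × 1.15 = 34.5, rounded up to 35.

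The stated 35 agrees with either within one person. Expected completers: 35 × 0.85 = 29.75, so about 30 remain and about 5 are lost.

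**2. Bias of the completer mean, without a dropout model.** Let k be the mean change of those lost as a multiple of the completers' mean change. The documents give no value for k, so it is an assumption and is shown as a range. With 30 completers and 5 lost:

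mean change of all 35, relative to completers = (30 + 5k) / 35; overstatement = 35 / (30 + 5k) − 1.

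| k | (30 + 5k)/35 | Completers against all enrolled |
|---|---|---|
| 1.5 | 1.071 | understate by 6.7% |
| 1 | 1.000 | no bias |
| 0.5 | 0.929 | overstate by 7.7% |
| 0 | 0.857 | overstate by 16.7% |
| −0.5 | 0.786 | overstate by 27.3% |
| −1 | 0.714 | overstate by 40.0% |

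The last two rows require those lost to get worse.

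**3. Bias under an explicit dropout model.** Assumptions, none from the documents: true pre-post change 0.30 SD, correlation between visits 0.7, 15% loss, log-odds of loss changing by 1 per SD of change. Simulated completer mean:
- poor responders leave: 0.40 SD;
- loss unrelated to response: 0.30 SD;
- good responders leave: 0.20 SD.

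With half that slope and poor responders leaving, it is 0.36 SD.

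**4. People lost from the pre-post contrast only because of the seven-month visit.** Take 15% total loss by seven months and deletion across all three visits. If a fraction p is already lost before posttest, the number with baseline and posttest but no follow-up is 35(1 − p) − 29.75:
- p = 0: 5.25
- p = 0.05: 3.5
- p = 0.10: 1.75
- p = 0.15: 0

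Between none and about five people with a usable pre-post pair would be discarded.

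**5. Does a mixed model repair this?** For anyone measured at posttest who stopped the sessions or missed only the last visit, yes: the baseline-to-posttest values are used. Where the posttest itself is missing because of poor response, it does so only slightly. Under the assumptions of step 3 (poor responders leave, 15% loss), a likelihood-based estimate using all baselines and available posttests gives 0.39 SD, against 0.40 for completers and a true 0.30.

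**The case against.** **The estimand is declared.** Section 5 states the hypothesis for completers, and the analysis matches it. There is also no randomisation to break. This is fair, but objective 1 in Section 2.1 is not limited to completers, and nothing else in the plan estimates the change for everyone who starts.

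**The study is exploratory and small.** This stands and lowers the severity. With 30 people, the 95% half-width for a mean change in units of its own SD is 2.045/√30 = 0.37, so sampling error exceeds the bias in most of the scenarios above.

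**The setting may limit loss.** All participants attend one centre, are measured in a familiar room there, and are guided by their own educators. Stopping the sessions need not mean a missing posttest, and loss at seven months may have nothing to do with response. This makes the size of the bias uncertain. It also means that posttest data on people who stop are likely to exist, and the stated analysis would not use them.

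**Stronger readings that the documents do not support.**
- A reader might infer that the change will be overstated. The article does not say who will leave or why, and the bias can be zero or negative.
- A reader might take deletion across all three visits as stated. It is inferred from the named tests; the text says only that missing data are not included.
- A reader might work out a very small analysis set by requiring attendance at all 11 sessions, or by assuming a rate of unusable heart-rate recordings. The article gives neither an attendance threshold nor such a rate. These details are commonly left to a fuller document, and their absence is not part of this point.

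What remains is a rule that the article does state, where a better one is available.

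**Conclusion.** The point holds as a risk of bias, not as a demonstrated overstatement. The stated analysis leaves out people who stop and, as the named tests ordinarily work, people who miss only the seven-month visit. With the planned 15% loss, completers would overstate the all-enrolled change by about 17% if the 5 people lost had no change, and by about 8% if they had half the completers' change. The bias is nil if loss is unrelated to response and reverses if better responders leave. Upward is the plausible direction, but that rests on an assumption about why people stop. Severity: should be fixed before the analysis, since the effect size feeds the decision on the next stage; the exploratory aim keeps it from being critical.

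**What to change.** - Make the main analysis all enrolled participants with a baseline value, whatever their attendance, using every available visit in a linear mixed model with visit as a factor.
- Keep the per-protocol analysis as secondary.
- Compare the baseline characteristics of those lost with those retained, and report the number lost and the reasons.
- Add a simple sensitivity analysis for missing posttests, for example with lost participants assumed unchanged. With 5 of 35 lost, this multiplies the completer change by 30/35 = 0.857. It is needed because the mixed model does not remove bias when the posttest is missing for poor response.

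Cost: a change of analysis wording, slightly more analysis work, and possibly a less favourable estimate. No extra visits or data are needed.

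### The planned omnibus test over three visits gives no signed pre-post estimate with a confidence interval, has no place for the announced covariates, and is imprecisely named

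*Protocol article*

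**What the plan says.** All of the following is in the Protocol article.

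- **Test** (6. Data Analysis Plan): "a one-way ANOVA test with a level of significance at 5% will be performed to compare mean differences in paired data across the time". This applies "When normal distribution is achieved". "Otherwise, the Friedman test will be used as its non-parametric alternative".
- **Covariates** (same paragraph): "Sex, age, medication, and degree of intellectual disability will be analyzed as potential confounders". No model that would hold them is named.
- **Effect size** (same paragraph): "Effect size based on Cohen’s d" is to be calculated. The pair of visits and the SD are not given.
- **Missing data** (same paragraph): the approach is per protocol, and missing data are left out.
- **Visits** (3. Data Collection Plan): baseline is two weeks before the intervention. The measures are repeated "right after finishing the last session (posttest) and seven months after completing the intervention (follow-up"). "The three data collection events will take place in the same room".
- **Delivery** (4.1): "Sessions will be carried out in groups of 6 to 9 participants and guided by a trained guide". The analysis section has no term for group.
- **Purpose** (2.1, 2.2 and 5): to estimate preliminary efficacy, to give an indication of the likely effect size from at least 30 people, and to test for higher quality of life, lower blood pressure and better coherence parameters.

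**The concern.** The analysis section fixes a test, a switching rule, a covariate list and an effect size, and these do not fit together.

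First, an ordinary one-way ANOVA is a test for independent groups. An analyst who follows the name literally leaves the between-person variance in the error term.

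Second, the repeated-measures version and Friedman both answer whether anything differs among three visits. The study needs to know by how much, and in which direction, outcomes moved from baseline to posttest. The omnibus result could be significant because of a change between posttest and follow-up alone.

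Third, neither test has room for sex, age, medication and disability grade.

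Fourth, both tests need all three visits. A person who lacks only the seven-month visit is therefore lost from the pre-post comparison as well.

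Fifth, choosing the test by a normality check lets different outcomes be analysed on different scales. A Cohen's d built on means and SDs is then still attached when normality has been rejected.

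At stake is the figure that the next stage of evaluation will be planned on.

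**Working it through.** **The plan's own figure.** The recruitment target of 35 comes from 30 people and 15% attrition: 30 × 1.15 = 34.5, and 35 × 0.85 = 29.75. It reproduces to within rounding and does not bear on this point.

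**Which ANOVA is meant.** The sentence speaks of paired data over time. Friedman is a within-person rank test, whereas the rank counterpart of an independent-groups one-way ANOVA is Kruskal-Wallis. The plan therefore means a one-way repeated-measures ANOVA.

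**What the name costs if followed literally.** Simulation with 20,000 runs per setting, n = 30, three visits and alpha 5%. The documents give no correlation or effect, so these are assumptions: visit correlation ρ from 0.3 to 0.8, a 0.5 SD shift at posttest, half of it kept at follow-up.

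| ρ | Independent one-way: type I error | Its power | Repeated-measures power | Friedman power |
|---|---|---|---|---|
| 0.3 | 0.015 | 0.33 | 0.51 | 0.40 |
| 0.5 | 0.003 | 0.29 | 0.66 | 0.54 |
| 0.7 | <0.001 | 0.22 | 0.88 | 0.76 |
| 0.8 | <0.001 | 0.18 | 0.97 | 0.91 |

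Type I error is about 0.05 for repeated measures and 0.053 to 0.058 for Friedman. Both respect the pairing.

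**What an estimate would deliver.** On the SD scale, the standard error of posttest minus baseline is √[2(1−ρ)/n]. With n = 30 and ρ = 0.7 this is √(0.6/30) = 0.141. With t = 2.045 on 29 df, the 95% interval is the estimate ± 0.29 SD. At ρ = 0.3 it is ± 0.44 and at ρ = 0.8 it is ± 0.24. The omnibus F and the Friedman statistic supply no such interval.

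**Loss from complete cases.** If all of the assumed 15% attrition fell between posttest and follow-up, 35 people would have both pre-post values but only about 30 would enter the test. The pre-post standard error would then be larger by a factor of 1/√0.85 = 1.08. This is an upper bound; if all losses come before posttest, the factor is 1.

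**Covariates.** In a complete-case within-person comparison, a trait that does not change takes the same value at every visit and drops out of each person's difference. Sex, baseline age and disability grade can modify the change but cannot confound it. Medication could confound if it changes, but section 3.1 describes its collection only before the intervention.

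**Cohen's d.** The ratio of d on the change-score SD to d on the baseline SD is 1/√[2(1−ρ)], with equal SDs at both visits. At ρ = 0.5 it is 1.00, at 0.7 it is 1.29 and at 0.8 it is 1.58. Required N scales with 1/d². Mistaking the first d for the second would multiply a later trial's N by 2(1−ρ): 1.0, 0.6 and 0.4 respectively.

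**Session groups.** Groups of 6 to 9 among 30 to 35 people make 4 or 5 groups. A constant group effect is the same at baseline and posttest, so it cancels from the change, and type I error stayed at 5% when this was simulated. Only a group effect that differs by visit matters. With an assumed share (ICC) of the within-person variance, and no group term in the analysis, type I error is:

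- repeated-measures ANOVA: 0.09 to 0.12 at ICC 0.05, and 0.14 to 0.19 at ICC 0.10;
- pre-post contrast: roughly 8% to 13% over the same ICCs.

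**The case against.** The strongest reply is that the sentence says the data are paired and names a within-person alternative, so nothing is ignored. That stands. A reader might infer that the plan throws away the pairing and most of its power, but the documents do not support this. The 22% belongs to the literal name only, and the intended test has about 88% power under the same assumptions.

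It can also be said that, with complete cases, a mixed model with a participant intercept gives essentially the same omnibus F test. This is true, so the gain lies in the contrasts, the intervals and the use of incomplete participants. An article may leave reporting detail to a fuller plan, but this one does name its tests, and those tests do not produce the estimate that it says it wants.

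The covariates might be examined separately, since the article does not say that they enter the ANOVA. That is possible, but no such analysis is named. A reader might go further and infer that the results will be confounded by sex, age or disability grade. They will not be, for the reason shown above.

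Finally, a reader might infer that people share one group and one guide for 11 weeks, so that clustering invalidates the tests. Fixed membership is not stated. Section 3.3 has each session report name the person guiding, and section 4.2 describes eighteen trained guides whose practice period includes guiding two of the sessions. Guides may therefore vary. The inflation figures also rest on assumed ICCs.

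**Conclusion.** The point holds at moderate severity. The test is misnamed. Read as intended, it still gives neither a direction nor a pre-post change with an interval, cannot carry the announced covariates, and loses people who miss only the last visit. The effect size is undefined as to contrast and SD, which could move a later trial's N by a factor of 0.4 to 1.0 for correlations of 0.8 down to 0.5.

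The power, precision and error figures rest on assumed correlations, shifts and ICCs. The points on direction, covariates and missing visits follow from the tests named and need no assumption. The matter is not critical: the study is exploratory and single-group, makes no power claim, and already lists its small sample and lack of a control group as limitations.

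**What to change.** Replace the test sentence in 6. Data Analysis Plan as follows.

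1. For each outcome, fit one linear mixed model with visit as a three-level factor and a participant random intercept, using all available visits of the people analysed. A random intercept assumes equal correlation between visits. Because the visits are unevenly spaced, check the result with an unstructured covariance.
2. Report posttest minus baseline as the main contrast and follow-up minus baseline as the second, each with a 95% confidence interval.
3. Standardise the effect on the baseline SD and give its interval.
4. Enter sex, age and disability grade as covariate-by-visit terms in exploratory analyses only. Enter medication as time-varying if it is recorded again at later visits.
5. If residuals are poor, use a bootstrap or permutation version of the same contrast in place of the normality switch.
6. Record each person's session group. If membership proves stable, add a group-by-visit term as a sensitivity analysis; a group intercept alone would not address the issue.

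At the least, rename the test a one-way repeated-measures ANOVA and add a sphericity correction. In one assumed non-spherical case the uncorrected type I error was 0.064.

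The cost is slightly more analysis work in standard R code, plus a record of group membership. Any group variance estimated from 4 or 5 groups will be imprecise and should be reported as such.

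### The parametric test for three visits of the same participants is named only as a one-way ANOVA; it should be named as a repeated-measures ANOVA so that it matches the paired data and its Friedman fallback

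*Protocol article*

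**What the plan says.** Section 6 of the protocol article (Data Analysis Plan) gives one rule for the quantitative efficacy outcomes. When the data are normal, "a one-way ANOVA test with a level of significance at 5% will be performed to compare mean differences in paired data across the time". The next sentence reads: "Otherwise, the Friedman test will be used as its non-parametric alternative". The section names no participant term, within-person factor or random effect.

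Section 3 (Data Collection Plan) fixes the data structure. There is a baseline two weeks before the intervention, and then "The same set of measures will be collected right after finishing the last session (posttest) and seven months after completing the intervention (follow-up"). It adds: "The three data collection events will take place in the same room". Each participant therefore contributes up to three correlated values per outcome.

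Section 2.2 bases the size on precision rather than power: "we considered that a minimum of 30 would be sufficient to give a reasonable indication of the likely effect size". It continues: "Assuming attrition of 15%, the study seeks to recruit 35 persons".

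**The concern.** Used without a qualifier, the term one-way ANOVA denotes the comparison of independent groups. Its rank counterpart is the Kruskal-Wallis test. Friedman ranks within each participant and is the counterpart of a one-way repeated-measures ANOVA. The named test and its stated alternative therefore do not belong together, and only the second fits three visits of the same people.

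An analyst who follows the name would leave the stable differences between people in the error term, although the design allows them to be removed. The test would then be conservative and could miss changes that the paired data show. Section 5 expects significant improvement in quality of life, blood pressure and coherence parameters. The Limitations section already concedes that significance across time may be hard to reach, and section 2.2 caps the pool at the 35 eligible people in the center. Losing the pairing would make that admitted weakness worse.

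**Working it through.** **The plan's own figure.** Section 2.2 goes from 30 to 35 recruits at 15% attrition. 35 × 0.85 = 29.75, about 30, so the figure reproduces to rounding (30/0.85 = 35.3). No power is stated, so there is none to reproduce. I use n = 30 completers.

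**Inputs from the article.** Three visits (section 3), alpha 0.05 (section 6), n = 30 (section 2.2).

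**Assumptions not in the article.** Equal correlation rho between any two visits, taken as 0, 0.3, 0.5 and 0.7. Normal outcomes with equal variance sigma² at each visit. A mean shift of d SD at one visit, with d = 0.3 or 0.5. A shift sustained over the last two visits gives the same power.

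**Error terms.** The total variance sigma² splits into a between-person part, rho × sigma², and a within-person part, (1 − rho) × sigma².
- Independent-groups ANOVA, F(2, 87): the expected error mean square is sigma².
- Repeated-measures ANOVA, F(2, 58): the expected error mean square is sigma²(1 − rho).
- Under no change, the expected mean square for visits is sigma²(1 − rho). The repeated-measures error term is therefore the right yardstick, and the other is too large by 1/(1 − rho): 1/0.7 = 1.4, 1/0.5 = 2.0 and 1/0.3 = 3.3.

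**Power of the repeated-measures test.** The noncentrality is n × Σ(μ_j − mean)² / [sigma²(1 − rho)]. For a shift d at one of three visits, the sum is (2/3)d². With n = 30 and d = 0.5 this is 30 × 0.1667/(1 − rho) = 5.0/(1 − rho), that is 7.1, 10.0 and 16.7 for rho 0.3, 0.5 and 0.7. The noncentral F distribution then gives 64%, 79% and 95%.

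**Both tests by simulation** (200,000 data sets per setting; the simulated repeated-measures power agrees with the noncentral F):

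| rho | Type I error, independent-groups | Type I error, repeated-measures | Power at d = 0.5, independent-groups v repeated-measures | Power at d = 0.3, independent-groups v repeated-measures |
|---|---|---|---|---|
| 0 | 5.0% | 5.0% | 49% v 48% | 20% v 20% |
| 0.3 | 1.5% | 5.0% | 46% v 64% | 14% v 27% |
| 0.5 | 0.4% | 4.9% | 43% v 79% | 9% v 36% |
| 0.7 | 0.02% | 5.0% | 39% v 95% | 4% v 56% |

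With 20,000 data sets per setting the type I errors come out at 1.6%, 0.4% and 0.03%, the same within simulation error.

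**Share of power lost**, as 1 − (independent-groups/repeated-measures), for rho 0.3, 0.5 and 0.7: 29%, 46% and 59% at d = 0.5; 49%, 75% and 92% at d = 0.3. With no correlation nothing is lost.

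**The case against.** The strongest reply is that the article never says the visits will be treated as independent groups. The sentence itself calls the data paired and makes time the factor. The fallback is Friedman, not Kruskal-Wallis. One-way means only one factor, and the proper within-person test is itself a one-way repeated-measures ANOVA. On that reading both branches are paired and only a qualifier is missing.

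Much of this stands. Three stronger readings are tempting, and the article does not support them:
- A reader might infer that the plan discards the pairing. The wording on pairing and the fallback point the other way.
- A reader might infer that a normality check decides whether an outcome gets a paired or an unpaired test. That follows only if the reference to paired data is ignored.
- A reader might infer that most of the power is lost. That needs the literal reading together with a correlation and an effect size that the article does not give. At d = 0.5 and rho 0.3 the loss is 29%.

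It is also fair that no power calculation depends on this test, that Cohen's d will be reported beside it, and that a conservative error does not create false claims of benefit. Covariance and sphericity detail is commonly left to an analysis plan, so its absence here is no fault.

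What does not stand is that inferable intent makes the wording correct. The article chose to name its test. The name, taken without qualification, is that of the wrong test for these data, and it conflicts with the next sentence.

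**Conclusion.** The point holds as an incorrect test name. A repeated-measures ANOVA was probably intended, but the text names the independent-groups test and pairs it with a fallback that belongs to a different test. An analyst who followed the name would run a conservative analysis. The direction is the same for any positive within-person correlation; the size in the table rests on equal correlation, 30 completers and the assumed rho and d.

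Severity is minor to moderate. The intent can be inferred, the study is an exploratory feasibility study whose size is not based on power, and the error could hide a change but not invent one.

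**What to change.** In section 6, replace the name of the parametric test with *one-way repeated-measures ANOVA (visit within participant, Greenhouse-Geisser correction)* and keep Friedman as its non-parametric alternative. The correction is a sensible companion because the visits are unevenly spaced: two weeks before the first session plus ten weeks to the eleventh is about 12 weeks from baseline to posttest, followed by seven months. Equal correlation between visits is then not assured.

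A linear mixed model with visit as a fixed effect is an optional equivalent. If it is used, specify either a random participant effect or an unstructured covariance over the three visits, not both, because the unstructured matrix already absorbs the random intercept. A mixed model would normally also use participants with a missing visit, so it would have to be reconciled with section 6, which leaves missing data out. The ANOVA wording avoids that.

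The cost is one phrase, with the same data and the same R software and no change to design or sample size. It should be made before the data are analysed so that the paired test is fixed in advance.
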